### Objective(s)

The objectives of the studies covered by this research protocol are:

To analyse the association between three instruments assessing reference symptoms and signs attributed to CS in patients with CLBP: CSI, QST and HRV.To analyse whether reference symptoms and signs attributed to CS are associated with functioning measurement outcomes in patients with CLBP. Specifically, to analyse the association between the three instruments assessing CS (CSI, QST and HRV) and: lifting capacity, aerobic capacity, PA levels and/or PA distribution or patterns, and patient-reported measurements.To analyse whether changes (between baseline and discharge) in reference symptoms and signs attributed to CS are related to changes in each of the functioning measurement outcomes in patients with CLBP. Specifically, to analyse whether decreases in CS described as: a lower CSI score, an increase in the pain thresholds (QST) and an increase in parasympathetic/vagal tone (HRV) are related to a better functioning described as: an increase in lifting capacity, an increase in aerobic capacity, an increase in PA levels and/or a change in PA distribution or patterns, and better outcome scores in patient-reported measurements.

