##### Quantitative sensory testing

A battery of standardised sensory tests quantifies the function of the somatosensory system. QST tests the characteristics of various sensation and nociceptive processes as representative of afferent nerve fibres and central pathways performance. The whole assessment lasts for 1 hour, and it consists of six sensory tests, which are measured in seven different predefined body locations: one training location to familiarise the patient with the tests, the most painful location (as pointed out by the patient), and five control locations. See online supplementary material 1 for full description of body locations. The standardised instructions of the sensory tests are read to the patient at each test performance. Of the tests, five consist of mechanical stimuli based on and performed following the QST examination of the German Research Network on Neuropathic Pain (DFNS) protocol,^32^ and one for CPM following the Nijmegen-Aalborg Screening QST protocol.^33 43^ Overall, the DFNS protocol has shown good test–retest (mean r=0.86) and interobserver reliability (mean r=0.83) in patients with affections in the somatosensory system either with or without pain.^44^ For the purpose of avoiding bias due to the order of the measurements and locations, a counterbalancing procedure is established, which accounts for the locations and the measurements to be made. This procedure provides three different assessment order groups, all of which begin with the measurements at the training location and end with the CPM test. An additional counterbalancing procedure has been made for allocating patients to these assessment order groups (either 1, 2, or 3). Every nine patients, a different allocation order is performed to ensure a similar amount of QST assessments per group. All assessors are trained in the QST protocol. The following sensory tests are performed:

10.1136/bmjopen-2019-031592.supp1Supplementary data

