### Analyses

Data records from the different tests and questionnaires will be collected and merged into one database. The database management will be done by the project team and handled according to the internal regulations of the UMCG. The analyses of the study will be performed with SPSS software version 22.0 (IBM).

Before any analysis, data will be prepared:

Variables need to be calculated: body mass index; DMA, WUR and CPM tests (see the Methods and analyses section, Measurements: CS measurements); PDI, Rand36-PF, PCS, BSI and IEQ questionnaires.HRV: data will be preprocessed to correct for any artefacts that may be present at the beginning or at the end of the recording.QST: the overall value of each sensory test is the mean at the most painful location and the five control locations together, provided that at most two locations are missing.To perform the analyses to respond to objective 3, delta scores are computed (difference in scores between baseline and discharge) for CS, functioning and those confounder variables which are also measured at the same time points as the main measurements.

Proxies of the main measurements were selected to perform analyses. CS variables are: the sum score of CSI part A and the RMSSD for HRV. For QST, no variables are predefined, variables that correlate most strongly with each of the functioning measures will be selected. Functioning variables are: the maximal weight lifted for lifting capacity, the VO_2_max/kg for the maximal aerobic capacity, the daily vector magnitude (VM) counts for PA and the average score of Rand36-PF for reported physical functioning.

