The presence of missing data will be checked. If a variable has more than 10% of missing data cases, its distribution will be further examined. When the distribution of missing data is missing completely at random, analyses with pairwise deletions are planned. If data are not missing completely at random, other suitable solutions will be applied such as multiple imputation.^91^ Regarding the presence of outliers, cases at 3 SD from the mean will be considered as outliers. Their influence will be measured using Cook’s distance and leverage values. When the outliers are not statistically influential and/or there is rationale for the outlier, no further actions are planned. The descriptive statistics of the sample characteristics and main test results will be at this point calculated; numerical variables as mean and SD in normally distributed data and as median and IQR (25–75)) in non-normally distributed data, and categorical variables as counts and percentage of each category level.

*Statistical approach for objective 1: to analyse the association between instruments assessing reference symptoms and signs attributed to CS.* Multiple partial correlation analyses will be performed and corrected for potential confounders. CS measurements will be the main variables and sex and age will be covariates. Additional covariates may enter the partial correlations based on their correlation coefficient with CS instruments and if p<0.01. Results will be reported as correlation coefficients (Pearson’s r and/or Spearman’s rho) and p values, with and without controlling for covariates. The significance level for all analyses is established at 0.01, to account for the potential type I error due to the multitude of partial correlation analyses.
*Statistical approach for objective 2: to analyse whether reference symptoms and signs attributed to CS are associated with functioning measurement outcomes.* First, multiple correlation analyses, followed by multiple regression analyses with data obtained at baseline, will be performed. Each of the main outcomes from functioning measurements will be introduced in the models as dependent variable, CS measurements as independent variables, and sex, age and other demographic characteristics and/or test-related variables as potential confounders and/or moderators.

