*Statistical approach for objective 3: to analyse whether changes (between baseline and discharge) in reference symptoms and signs attributed to CS are related to changes in each of the functioning measurement outcomes.* A similar approach to objective 2 will be performed: first, multiple correlation analyses will be performed with data obtained at baseline and discharge, followed by multiple correlation analyses using delta scores of the data and, finally, multiple regression analyses again using delta scores. As in objective 2, each of the main outcomes from functioning measurements will be introduced in the models as dependent variable, CS measurements as independent variables, and sex, age and other demographic characteristics and/or test-related variables as potential confounders and/or moderators.

Confounders entering the final models of objectives 2 and 3 will be selected based on their partial correlation coefficient with CS and functioning, and they will be included if p≤0.10. All multiple regression models will have the assumptions checked. Results of objectives 2 and 3 will be reported as coefficient (b), CIs (95% CI), p values and explained variance, with and without controlling for confounders and/or moderators. Due to the large amount of correlation analyses and the risk of high type I error, a stricter significance level for correlation analyses is established, p<0.01. For multiple regression analyses the significance level is at 0.05.

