There are circumstances that might have influenced the results, in spite of the team’s efforts to obtain the most extensive insights of CS and its association with functioning. To begin with, it should be considered that patients participating in the study are volunteers. Moreover, the exclusion criteria, despite being based on patients’ files, are also dependent on doctor’s judgement. The impact of these circumstances is so far unknown to the authors. Likewise, given the CAU design of the study the choice of measurements has to be feasible and compatible with the regular clinical procedures. As a consequence, the functional MRI, a commonly mentioned instrument to measure CS, could not be performed in the study. The HRV, on the other hand, although less often used, can be an insightful and innovative approach to the assessment of one of the indicators of CS. Additionally, the sample sizes are estimated a priori for the analyses due to insufficient previous studies and, therefore, they are of exploratory nature and used as a guide. Also, despite the efforts of the team to promote the study participation and participant retention, it is likely that patient recruitment may be slower than anticipated and that the patient may not have a complete follow-up. However, since the measurement period is ample, the calculations are vigilantly made with generous margins (see the Methods and analyses section, Sample size), and the literature related to the topic has shown smaller sample sizes.^25 28 110^ We remain positive about the sample size and expect to have more than enough participants to perform analyses with sufficient power. Also, for comparability purposes, measurements are planned to take place within 3 weeks from the Pain Rehabilitation team’s baseline and discharge assessments. The CSI, PDI and psychological screening questionnaires during baseline assessment are sent to be filled up 6 weeks before the rest of the measurements are obtained, a time distance due to waiting list time. Measurements are expected to be comparable to the rest of measurements at baseline, since no important changes are foreseen in patients regarding medication, surgery or personal conditions during this time, and questionnaires have shown to have good clinimetric properties. As opposed to the limitations presented, given the large amount of correlations in the multiple correlation analyses and the risk of type I error, a more strict significance level was applied, that is, 0.01. Also, for the QST the proxy will be selected per functioning outcome to obtain the most informative somatosensory measurement for each of the functioning measurements. We are confident that the results obtained will provide meaningful and valuable information.

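### The QST predictor is chosen by its correlation with each functioning outcome and then tested on the same patients at an unadjusted 0.05, so its null false-positive rate is about 16–25% per outcome

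*Protocol article*

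**What the plan says.** The Analyses section names fixed proxies for two of the three CS instruments: the CSI part A sum score and RMSSD. For the third it states: "For QST, no variables are predefined, variables that correlate most strongly with each of the functioning measures will be selected". The Discussion repeats the rule as a benefit: "for the QST the proxy will be selected per functioning outcome to obtain the most informative somatosensory measurement".

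There are six candidates. The QST section says of the assessment that "it consists of six sensory tests" (DMA, MPT, WUR, MDT, PPT and CPM), and the Analyses section reduces each test to one number: "the overall value of each sensory test is the mean at the most painful location and the five control locations together".

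For objective 2 the order of work is: "First, multiple correlation analyses, followed by multiple regression analyses with data obtained at baseline, will be performed". Objective 3 follows the same order with change scores. Two significance levels are set. For correlations, "a stricter significance level for correlation analyses is established, p<0.01". For the models that answer objectives 2 and 3, "For multiple regression analyses the significance level is at 0.05". The models are reported with coefficient, 95% CI, p value and explained variance. No sample split, resampling or adjustment for the choice of QST test is described.

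Objective 3 words the expected QST improvement as "an increase in the pain thresholds (QST".

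**The concern.** A variable picked because it has the largest correlation with an outcome, and then tested against that outcome in the same patients, has already passed a best-of-six contest. The ordinary t test and CI assume that it was named beforehand. The p value is therefore too small, the interval sits too far from zero, and the explained variance is too high. The 0.01 level does not reach this step, because the article assigns it to the correlations and sets 0.05 for the regressions.

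At stake is whether a reported QST–functioning association can be believed, for four functioning outcomes in each of two objectives. There is also a mismatch with the stated hypothesis. MPT and PPT are pain thresholds. MDT is a touch-detection threshold, DMA and WUR are ratios of pain ratings, and CPM is a percentage change in PPT. The rule can therefore put into the objective 3 model a variable that its hypothesis does not mention.

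**Working it through.** **The plan's own figure.** The Sample size section gives 77 patients for objectives 2 and 3 (medium effect, eight predictors, three of them CS measurements, α 0.05, power 0.8), then 110 for about 30% loss. I take medium as f² = 0.15, a convention that the article does not state. A noncentral F test of 3 of 8 predictors, with λ = 0.15·N and N − 9 denominator degrees of freedom, first reaches 80% power at N = 77. Then 77 / (1 − 0.30) = 110. Both figures reproduce. They assume that the three CS predictors are tested at a true 0.05.

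**Analytic ceiling.** For six independent tests each at 0.05, the chance that at least one is significant is 1 − 0.95^6 = 26.5%. For five it is 1 − 0.95^5 = 22.6%.

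**Simulation under the null.** The outcome is independent of all predictors, and the six QST tests share a common correlation ρ. The test with the largest absolute correlation is selected. It enters a least-squares model with CSI, RMSSD, sex, age and three further covariates (eight predictors), and its coefficient is tested at two-sided 0.05. There are 8,000 runs per cell; the Monte Carlo standard error near 20% is √(0.2 × 0.8 / 8000) ≈ 0.4 percentage points. The article gives no value for ρ, so the range is an assumption.

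| ρ among tests | N = 77, six candidates | N = 110, six candidates |
|---|---|---|
| 0 | 24.6% | 24.8% |
| 0.2 | 23.4% | 24.1% |
| 0.3 | 23.0% | 23.2% |
| 0.5 | 19.4% | 20.0% |
| 0.7 | 16.0% | 16.9% |
| one prespecified test | 5.1% | 5.2% |

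With five usable candidates and ρ from 0 to 0.5, the rate is 17.5–21.8%. The joint test of the three CS predictors, with six candidates and the same ρ, rises from 5% to about 12–14%.

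**Size of the coefficient under the null.** The mean absolute standardised coefficient is 0.15–0.16 after selection against 0.08 for a fixed test (N = 110), and 0.18–0.19 against 0.10 (N = 77), for ρ of about 0 to 0.5. It is nearly doubled.

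**Size when effects are real.**
- If one test has a true standardised effect of 0.30, the selected coefficient averages 0.30–0.32 in absolute value, so inflation is almost nil.
- If one test has a true effect of 0.20, it averages 0.22–0.24.
- If all six tests truly correlate 0.20 with the outcome, the selected correlation averages 0.28–0.31 at N = 110. At the top, 0.31 / 0.20 = 1.55, or about 55%. At N = 77 the top value is 0.33, or about 65%. For weaker true correlations the relative inflation is larger.

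**The case against.** **The 0.01 level for correlations could act as a filter.** Selection runs through the correlation analyses, which carry p<0.01. If the QST test had to reach that level before entering the model, the simulated false-positive rate at N = 110 would be 5.3–5.4%. This is the strongest reply. However, the article does not make 0.01 an entry condition for QST; it says only that the strongest correlates are selected. A filter would also leave the coefficient and its CI biased, because only large sample correlations would pass.

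**The limits are acknowledged.** The strengths and limitations list concedes that the choice of measurements may influence results. That is disclosure without correction. The word exploratory is applied to the sample size estimates, not to the regression p values.

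**The simulation inputs are not in the article.** This stands. The inter-test correlation is unknown. The Analyses section speaks of variables in the plural while the Discussion speaks of a single proxy, so one selected test per outcome is also an assumption. DMA and WUR are missing at any location where the first rating is 0, so fewer than six tests may be usable. The range above allows for ρ up to 0.7 and for five candidates.

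**Stronger readings that the article does not support.**
- That effects will in general be doubled. Near-doubling describes the absolute coefficient under the null; with real effects the inflation depends on the scenario.
- That objective 1 has no usable QST variable. Its text refers to a multitude of partial correlations, which fits correlating every QST test.
- That QST is unfairly favoured in a contest with CSI and RMSSD. No objective ranks the instruments, and the Introduction calls them complementary.

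**Conclusion.** The point holds. It rests on a rule the article states, not on an omission that a fuller plan might fill. If one of six tests is selected, the QST coefficient has a null false-positive rate of about 16–25% per outcome (assumed inter-test correlation 0.7 down to 0), or about 17–22% with five usable tests and correlations of 0 to 0.5. The nominal rate is 5%.

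The selected coefficient is biased away from zero. Its mean absolute value is nearly doubled under the null. With real effects the inflation runs from almost nil to about 55% at N = 110 in the scenarios with true values of 0.20 to 0.30, and somewhat more at N = 77.

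The rate is per outcome and concerns the QST coefficient. A reader might infer that CSI and RMSSD share the problem, but those variables are fixed in advance and not selected this way. A reader might also compound the rate over the four outcomes; that would need an assumption about how the outcomes are related, which the article does not supply. The mismatch with pain thresholds applies to objective 3 only, since objective 2 refers to QST in general.

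**What to change.** Before any outcome is analysed, name one QST variable, or one composite, and use it for all functioning outcomes in objectives 2 and 3. For objective 3 a single variable should be a pain threshold, to match the stated hypothesis. A composite needs a written rule for the sign of each component (the direction the article gives for CPM should be confirmed first) and for patients whose DMA or WUR ratio is missing. Report the remaining QST tests as exploratory.

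If selection by correlation is kept, take the p value from a permutation test of the maximum over the candidate tests, or test the selected QST coefficient at about 0.05 / 6 = 0.0083. Take the CI from a bootstrap that repeats the selection in every resample. State also how many QST tests may be selected per outcome.

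The cost is analysis wording; no new data are needed. A fixed variable may not be the best-fitting one for each outcome, and a single pain threshold moves temporal summation and CPM to exploratory status. The selection-aware route keeps all six tests in play but has somewhat less power.

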### Sample size

Due to the limited amount of relevant previous or similar studies, the sample sizes for the several analyses described in this research protocol are estimated a priori with GPower (G*Power for Windows, Version 3.1.9.2), and are exploratory as a result.

The following sample size calculations, as well as the planned statistical analyses later described, will be performed with proxies for the main variables. Additionally, due to the influence of patient’s sex and age in the assessment outcomes, all analyses will include these variables for a moderator effect.

*Sample size for objective 1: to analyse the association between instruments assessing reference symptoms and signs attributed to CS.* Correlation analyses will be performed for this objective. The correlation between the different CS measurements is expected to be weak as reported on associations between certain CS measures and tests.^24^ For a correlation coefficient of 0.25, an α error probability of 0.05 and a power of 0.8, a minimum sample size of 97 is calculated.
*Sample size for objective 2: to analyse whether reference symptoms and signs attributed to CS are associated with functioning measurement outcomes; and for objective 3: to analyse whether changes (between baseline and discharge) in reference symptoms and signs attributed to CS are related to changes in each of the functioning measurement outcomes*. Multiple regression analyses will be performed for objectives 2 and 3. Based on the associations between CSI and psychosocial and cognitive behavioural factors,^24 25^ the effect size is hypothesised to be medium. Since minimally three CS measurements are tested with sex and age required as independent variables, and controlled for the confounding effect of other demographic and test-related variables, eight predictors are foreseen. Taking into account the factors mentioned above, the sample size calculation results in a minimum of 77 patients, calculated with an α error probability of 0.05 and a power of 0.8. Finally, patients measured at discharge could be about 30% less than at baseline due to either not following the interdisciplinary rehabilitation programme or personal reasons; a sample size of 110 patients may be required in this scenario.

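### The rule for choosing the QST test states no adjustment for sex and age, so where functioning is strongly sex-linked it can select a sex-linked test over the one related to functioning

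*Protocol article*

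**What the plan says.** The Analyses section fixes one proxy each for CSI and HRV but not for QST: "For QST, no variables are predefined, variables that correlate most strongly with each of the functioning measures will be selected". The Discussion repeats this: "for the QST the proxy will be selected per functioning outcome to obtain the most informative somatosensory measurement for each of the functioning measurements". Neither sentence mentions sex, age or any other covariate.

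The candidates are the tests of the QST battery: "it consists of six sensory tests, which are measured in seven different predefined body locations". These are DMA, MPT, WUR, MDT, PPT and CPM.

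The chosen test is then used in regressions with "CS measurements as independent variables, and sex, age and other demographic characteristics and/or test-related variables as potential confounders and/or moderators". The Sample size section counts sex and age among the required independent variables. It also states, on account of the influence of the patient's "sex and age in the assessment outcomes, all analyses will include these variables for a moderator effect".

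For objective 2 the order of work is: "First, multiple correlation analyses, followed by multiple regression analyses with data obtained at baseline, will be performed". For objective 1 the same section says: "Multiple partial correlation analyses will be performed and corrected for potential confounders". Confounders for objectives 2 and 3 are also chosen on a partial correlation coefficient. The QST rule does not carry that qualifier.

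**The concern.** The selection step and the model answer different questions. An unadjusted correlation mixes the association within sex and age groups with the part that arises only because both variables differ by sex or age. The regression coefficient keeps the first part alone.

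A sensory test that differs between men and women, but has no association with functioning within either sex, can still correlate with functioning. If it wins the ranking, little is left once sex is in the model. The test that is related to functioning within sex may then be passed over. This would work against the Discussion's aim of finding the most informative somatosensory measure for each outcome, and a null QST coefficient could be reported although another collected test is associated with functioning.

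The precondition is the protocol's own premise that sex and age influence the assessments. How strong that influence is, and for which of the four functioning outcomes, is not given.

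**Working it through.** **The plan's own figures.** A medium effect is taken as f² = 0.15 (assumption; the figure is not printed). With 3 tested of 8 predictors, alpha 0.05 and power 0.80, the noncentral F calculation gives N = 77 (power 0.800), as stated. Then 77 / (1 − 0.30) = 110, also as stated. So N = 110 at baseline and 77 at discharge are the sizes to examine.

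**When the wrong test wins.** Let ry be the correlation of sex with functioning and rq that of sex with a test A that is linked to sex only. Let pr be the partial correlation with functioning of a test B that is not linked to sex. The unadjusted population correlations are:
- test A: ry × rq
- test B: pr × √(1 − ry²)

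Test A overtakes test B only if rq > pr × √(1 − ry²) / ry. All values are assumed:

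| ry | limit for rq, pr = 0.25 | limit for rq, pr = 0.30 |
|---|---|---|
| 0.7 | 0.26 | 0.31 |
| 0.6 | 0.33 | 0.40 |
| 0.5 | 0.43 | 0.52 |
| 0.4 | 0.57 | 0.69 |
| 0.3 | 0.79 | 0.95 |

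With functioning strongly sex-linked, a moderate sex difference in the test is enough. With ry near 0.3, an implausibly large one is needed.

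**Simulation, N = 110.** Assumptions: half women, six independent tests (A, B and four null), pr = 0.25, selected coefficient tested at 0.05 with sex in the model. Sex differences are in within-sex SD units; with half women, r = (d/2) / √(1 + d²/4). For d = 1.5 this is 0.75 / 1.25 = 0.60, and for d = 0.7 it is 0.35 / 1.059 = 0.33. The unadjusted correlations are then 0.60 × 0.33 = 0.20 for A and 0.25 × 0.80 = 0.20 for B, a tie.

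| Sex difference: functioning / test A | B selected and significant, unadjusted ranking | same, ranking given sex |
|---|---|---|
| 2.0 / 1.0 SD | 11% | 71% |
| 1.5 / 0.7 SD | 41% | 71% |
| 1.0 / 0.4 SD | 65% | 72% |
| 0.5 SD in functioning | 70–71% | 72–73% |

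In the 1.5 / 0.7 case unadjusted ranking picks A in 44% and B in 45% of runs. Simulation error is about one percentage point.

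**Second set-up, with age, CSI and RMSSD also in the model.** For (ry, rq, pr) = (0.6, 0.4, 0.3), B is selected and significant in 47% against 87% at N = 110, and in 43% against 73% at N = 77. For (0.3, 0.3, 0.3) at N = 110 it is 83% against 87%.

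**False positives when no test is related given sex.** Adjusted ranking takes the largest of six adjusted associations, so the 0.05 test rejects in about 1 − 0.95⁶ = 26.5% of studies; simulation gives 26–27%. Unadjusted ranking gives about 11% in the 1.5 / 0.7 case and 10–27% over the settings run. It is lower because the rule then often settles on the sex-linked test rather than on the largest adjusted association. The 71% and 41% above are therefore not at equal error rates.

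**With 0.05/6 = 0.0083 for the selected coefficient**, detection in the 1.5 / 0.7 case is 49% under adjusted ranking against 33% under unadjusted ranking. The advantage remains.

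**The case against.** **The text never says the ranking is unadjusted.** The Abstract and the Sample size section call the objective 1 analysis simply correlation, although the Analyses section makes it partial. An unqualified word therefore proves little, and the sentence that all analyses include sex and age could be read to cover the selection. This stands in part: unadjusted ranking is the natural reading, not a stated one. But that sentence speaks of a moderator effect, which is an interaction and not an adjusted ranking. At best two analysts could select different tests.

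**More than one QST test might enter.** The Analyses section uses the plural and the Sample size section foresees at least three CS measurements. The Discussion speaks of one proxy per outcome. A reader might infer that the related test is certain to be left out; the documents do not settle that. The correlation analyses that precede the regressions, and the reporting with and without confounders, also give some further information, though they would not show that another test was better in the adjusted model.

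**The scenario is constructed.** The tests are independent, one is linked to sex only and one not at all. A reader might infer that the rule generally tends to pick the most sex-linked test. The calculations do not bear this out: the 1.5 / 0.7 case is a near tie, and at 1.0 / 0.4 SD the related test is picked far more often. Nor do the documents show that lifting capacity or VO₂max/kg are strongly sex-linked in these patients.

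**Adjusted ranking alone raises false positives.** Correct, and it determines the form of the fix.

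**Limits are disclosed.** The article calls its sample sizes exploratory and says that the selection of measurements may influence results. That does not resolve which correlation is meant.

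**Conclusion.** The point holds in a conditional form. The QST rule states no adjustment for sex and age, while the models that use the selected test contain both. Where functioning is strongly sex- or age-linked, the rule can select a sex-linked test over the one related to functioning given sex and age.

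Under the assumed values at N = 110, the chance of selecting the related test and finding it significant falls from about 71% to 41% or, in the most extreme case, 11%. It falls from 72% to 65% with smaller sex differences, and hardly at all when functioning differs by 0.5 SD or less. These sizes rest entirely on assumed sex differences; age was not varied as a source of confounding.

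The concern is mainly objective 2. A stable sex difference largely cancels in delta scores if selection for objective 3 is made on those; the article does not say whether it is. The point merits a correction to the rule but does not undermine the study.

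**What to change.** In the Analyses section, state that the QST tests are ranked by their partial correlation with each functioning measure given sex and age, computed on delta scores for objective 3. State that one test per outcome is selected, if that is meant. Test the selected coefficient with allowance for choosing among six candidates, for example at 0.05/6 or with a max-statistic permutation test that repeats the selection in each permutation. Adjusted ranking should not be adopted without this allowance. Naming the QST variable per outcome in advance would remove the selection question altogether.

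The cost is a change to one rule, a little more analysis work and a stricter threshold for the QST coefficient. No new data are needed, and partial correlation is already planned for objective 1. In the 1.5 / 0.7 SD case the stricter threshold lowers detection under adjusted ranking from 71% to 49%, which is the price of controlling the false-positive rate.
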